## Abstract

**Background and Aims:**

Polycystic ovarian syndrome, with a mean incidence of 5–10, is the most common endocrine disorder affecting women of reproductive age. These patients suffer from a wide range of symptoms that are inversely related to their resilience and quality of life. Thus, this study protocol was prepared to determine the effect of hypnotherapy intervention on the resilience of patients with polycystic ovary syndrome.

**Methods:**

The current study protocol is a randomized clinical trial. In total, 56 women diagnosed with polycystic ovarian syndrome will be invited to participate in a 6‐week intervention. After allocating the samples to two control and intervention groups using a block randomized design, for each subject in the intervention group, 6 weekly sessions of hypnotherapy will be held for 40–60 min, and for the control group, routine care will be provided. In this study, the level of patient resilience will be measured as the primary outcome using the Connor‐Davidson Resilience Scale (CD‐RIS). Analysis will be conducted using SPSS V.26. To compare variables between intervention and control groups according to the qualitatively and quantitatively variable nature, the *χ*
^2^ test (if the default is not established, Fisher's exact test) and *t*‐test of two independent samples, analysis of variance, or its non‐parametric equivalent (Mann–Whitney and Kruskal–Wallis) will be used, respectively.

**Discussion:**

This plan focuses on the resilience and quality of life in women with polycystic ovarian syndrome. Considering that hypnotherapy is safe and relatively inexpensive, and has almost no side effects, it is very important to determine whether women with polycystic ovary syndrome could benefit from this psychological technique.

**Trial Registration:**

Iranian Clinical Trial Register IRCT20161126031117N12; Registered V1.0 on May 4, 2022.

## Background

1

Polycystic Ovarian Syndrome (PCOS), also known as Stein–Leventhal syndrome, is the most common endocrine disorder affecting women of reproductive age, with a mean incidence of 5%–10% [1, 2]. Women with PCOS display various symptoms, including amenorrhea, oligomenorrhea, hirsutism, subfertility or infertility, anovulation, weight gain or obesity, acne vulgaris, and androgenic alopecia [3]. As per the updated Rotterdam Criteria established by the European Society of Human Reproduction and Embryology, along with the American Society for Reproductive Medicine, a diagnosis of PCOS requires meeting at least two out of the three criteria [2, 3]. These criteria include anovulation, excess androgen levels, and polycystic ovarian appearance observed through ultrasound evaluation [4, 5, 6].

The prevalence of PCOS is relatively high in Iran (11.4%) [7]. During the reproductive years, the primary issue faced by the patient is infertility along with irregular ovulation [8]. This syndrome is the leading reason for roughly 75% of infertility resulting from an absence of ovulation [9]. Individuals with PCOS encounter higher risks of endometrial and ovarian cancer [10], delayed menopause [11], type 2 diabetes, hypertension, lipid abnormalities, cardiovascular issues [12, 13], depressive and anxious states [14], social anxiety [15], eating disorders [16], suicide attempts [17], and bipolar disorder [18]. According to the previous studies, women with higher resilience face a lower risk of irregular menstruation. Resilience could be described as the capability to bounce back from stress, maintaining consistent levels of mental and physical performance despite stressors, or as the enhancement of health and adaptability, irrespective of the stress levels individuals encounter [19]. Normal women have higher endurance compared to women with ovarian cysts [20]. In addition, studies indicate that the consequences and complications associated with PCOS cause psychological damage and a notable decline in both quality of life and health‐related quality of life for women affected by this condition [1, 21]. Therefore, the quality of life for women with PCOS has been noted to be lower than that of women without the condition [22] and even inferior to individuals with certain illnesses like diabetes, asthma, and epilepsy [23]. Furthermore, these individuals have a significant risk of experiencing depression and anxiety disorders [24].

So, PCOS is a long‐term condition that impacts both the physical and mental well‐being of those affected, significantly diminishing their quality of life [25]. Currently, various methods including pharmacological methods such as Metformin [26], Letrozole and Clomiphene Citrate [27], Finasteride [28], etc. as well as nonpharmacological methods such as cognitive‐behavioral therapy [29, 30], acupuncture [31], lifestyle management [32, 33], relaxation [34], acceptance and commitment therapy [35], yoga [36], etc. are used to reduce the complications caused by PCOS. One of the nonpharmacological methods used in gynecological diseases is hypnotherapy [37, 38]. Hypnosis is a normal occurrence that nearly everyone goes through occasionally. Hypnotic trance states resemble daydreaming and rely on the notion that many individuals are somewhat suggestible [39]. Hypnotherapy is a treatment that employs a hypnotic approach to access an individual's subconscious mind. Hypnotherapy in surgery can provide a comfortable and relaxing experience for patients. Hypnotherapy, in principle, can evoke sensations of joy, contentment, security, and ease, enabling an individual to feel empowered to combat or lessen their anxiety levels [40]. Hypnosis is secure and fairly affordable, can be learned by many determined individuals to some extent, and has almost no side effects [39]. According to the extensive search that has been done in the available databases, so far, no clinical trial study has been conducted about the impact of hypnosis on the psychological complications of polycystic ovary syndrome in Iran and international studies. For this reason, we tried to design a study to investigate the impact of hypnotherapy treatment on the resilience of individuals with polycystic ovary syndrome.

## Methods

2

### Objectives

2.1

The primary objective of this study is to assess the impact of hypnotherapy on the resilience of individuals suffering from polycystic ovary syndrome (PCOS). The particular aims of this study are to assess and contrast the levels of resilience, quality of life, anxiety, and depression in both the control and intervention groups before the intervention, right after the intervention, and 4 weeks post‐intervention.

### Study Design

2.2

This study is a randomized clinical trial consisting of two parallel groups of intervention and control.

### Study Registration

2.3

The researcher received their code after registering the project in the Ethics Committee of Mazandaran University of Medical Sciences (IR.MAZUMS.REC.1400.11670) and registering it in the Clinical Trial Registration Center of Iran (IRCT20161126031117N12).

### Study Setting and Participants

2.4

In this study, the research community is women with polycystic ovarian syndrome, and the research setting is healthcare centers and gynecological and midwifery offices from different parts of Tehran, Iran. These settings are usually staffed by healthcare providers, gynecologists, and midwives to whom different patients with different socioeconomic statuses and educational backgrounds would refer. Recruitment will occur through advertisements placed in waiting rooms in healthcare centers, gynecological and midwifery offices in Tehran, as well as media outlets.

#### Inclusion and Exclusion Criteria

2.4.1

The inclusion criteria will include 19–49‐year‐old Iranian women with confirmed polycystic ovarian syndrome according to Rotterdam criteria who have attended to visit for the first time because of this disease, not being infertile, and undergoing assisted reproductive therapy, literacy in reading and writing in Persian, and being satisfied to participate in the research. In addition, exclusion criteria will be an occurrence of any kind of acute complication affecting the quality of life and resilience during the intervention, (such as the death of important people in a person's life) [41], being suffering from other endocrine diseases or any other chronic diseases which affect patient's quality of life; for instance, chronic debilitating liver and kidney diseases [41], being psychotic and having serious thoughts of harm to oneself and others (recognized by a psychiatrist) [42], history of seizures [42], using psychotropic drugs and any kind of drug abuse [30, 41] and participating in similar training sessions [41].

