### Blinding

2.7

It will be impossible to keep participants blind during the intervention process, as a result of the nature of the intervention [44]. Blinding will be done at the assessor level [45]. In this way, after concluding the work, the research colleague hands over the questionnaires to the samples, and after completing the questionnaire, a box will be placed there, and the participants will put the completed questionnaire in the box. Groups are named A and B. The statistical analyst is also blinded, and at the end of the analysis, the coded groups will be identified [44, 45, 46]. Figure 1 is the CONSORT flow diagram and includes the calculation of the numbers of eligible, screened, enrolled, and analyzed participants.

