#### Data Collection Tools

2.9.1

In this study, the level of patient resilience will be measured as the primary outcome using the Connor‐Davidson Resilience Scale (CD‐RIS). The reliability and validity of the Persian Resilience Scale have been investigated and validated in preliminary studies in patient and normal samples. Mohammadi used Cronbach's alpha coefficient; the reliability scale reached 0.89, and the worth of each item alongside the overall score using the correlation coefficient ranged from 0.41 to 0.64 [47]. Samani and Sahragard, in a study on students in Shiraz, achieved scale reliability through Cronbach's alpha coefficient of 0.87 [48].

Additionally, the quality of life of the patients (as the secondary outcome) will be measured using the PCOS Health‐Related Quality of Life Questionnaire (PCOSQ). Amini et al. showed that the Iranian version of PCOSQ has acceptable validity and reliability and is an appropriate tool for measuring the quality of life of patients with polycystic ovary syndrome. To assess the reliability of the questionnaire, they employed the method of evaluating the internal consistency of the instrument. The findings demonstrate that the Cronbach's alpha coefficient for the entire questionnaire was 0.90, for emotional aspects it was 0.80, for hirsutism it was 0.87, for weight it was 0.77, for infertility issues it was 0.84, and for menstrual issues it was 0.52. In addition to testing the validity of the questionnaire, a type of validation, namely item‐level correlation and comparison between known groups, was used. So, each question shows the highest correlation coefficient with its relevancy domain, and all coefficients are greater than 0.4 [49].

Eventually, their anxiety and depression (as the secondary outcome) will be evaluated using the Hospital Anxiety and Depression Scale (HADS). Kaviani et al. showed in their research that the HADS scale and subscales of anxiety and depression have good validity, reliability, and internal consistency with a Cronbach's alpha coefficient of 0.07 for the seven items of the depression scale, and 0.85 for the seven items under the anxiety scale [50].

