### Interventions

2.10

After allocating the samples to two control and intervention groups, they will be provided with the questionnaires. Then, patients of both groups receive standard treatments related to women with PCOS (including oral contraceptives, spironolactone, and metformin) [30, 51] and will be visited and treated by a gynecologist. Patients will also be recommended to follow a diet of their choice with an intake of 1500–1800 kcal per day [29], as well as a gentle aerobic exercise activity of 150 min per week [52] during the study. In addition, they should not use other relaxation methods and counseling sessions during the research. Also, the participants will be asked not to use cosmetic procedures (including laser and Botox, etc.) during the study, and they will be asked in each session, and if they are used, it will be recorded.

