### Protocol Deviation

2.11

Deviations or protocol violations may have occurred in this study and will be reported. An instance of deviation in a procedure is a follow‐up appointment occurring at a slightly varied time frame than mandated by the protocol; patients with these deviations will be incorporated into the intention‐to‐treat analysis. All study subjects randomly assigned to the studied groups during randomization processes, regardless of the type of intervention received during the study, their violation of protocol, discontinuation, and withdrawal from participating in the study, as well as all cases that occurred after randomization, will be included in the intention‐to‐treat analysis.

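### An exclusion criterion that can only be met after randomisation, and is tied to the primary outcome, is not reconciled with the intention-to-treat rule

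*Protocol article*

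**What the plan says.** Section 2.4.1 of the protocol article opens its exclusion list with this rule: "exclusion criteria will be an occurrence of any kind of acute complication affecting the quality of life and resilience during the intervention". The example given is bereavement ("such as the death of important people in a person's life").

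Section 2.10 gives the order of events: "After allocating the samples to two control and intervention groups, they will be provided with the questionnaires". Standard treatment and the six weekly sessions come after that.

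Section 2.11 defines the analysis set. All randomised women enter the intention-to-treat analysis, "regardless of the type of intervention received during the study, their violation of protocol, discontinuation, and withdrawal from participating in the study". The same sentence adds events after allocation: "as well as all cases that occurred after randomization".

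Three further statements bear on the consequences:
- Section 2.9.1 makes resilience the primary outcome: "the level of patient resilience will be measured as the primary outcome using the Connor". Quality of life is a secondary outcome.
- Section 2.7 says of the women themselves: "It will be impossible to keep participants blind during the intervention process".
- Section 2.16 concedes that the hypnotherapy arm has considerably more contact with the clinical team than the control arm.

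**The concern.** An exclusion criterion normally decides who is randomised. This one cannot, because its trigger occurs during an intervention that starts after allocation. It can act only as a rule for removing women already in the trial, and Section 2.11 says that such women are kept.

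The trigger makes this more than a matter of tidiness. It is defined by an effect on resilience and quality of life, which are the primary outcome and a secondary outcome. It is also open-ended: bereavement is only an example, so someone must judge whether an event qualifies. Section 2.9.2 says that the coordinator who documents attrition knows the allocation, and Section 2.16 accepts that the researcher does too. With more contact in the hypnotherapy arm, qualifying events may be noticed more often there.

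If exclusion means leaving follow-up or analysis, the women compared at the end are no longer all those randomised. The selection would depend on something close to the outcome and could differ by arm.

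**Working it through.** **1. The sections side by side**

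| Question | Section 2.4.1 | Section 2.11 |
|---|---|---|
| When does the event occur? | During the intervention, hence after allocation (Section 2.10) | After randomisation |
| What happens to the woman? | Excluded; follow-up and analysis not mentioned | Included in the intention-to-treat analysis |

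Both can hold only if exclusion means something less than leaving the study, for example stopping sessions while outcome collection continues. The article does not say so.

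**2. The plan's own figures**

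Section 2.5.1 gives means and SDs of 48.17 (20.61) for control and 69.80 (23.38) for intervention, a type 1 error of 0.05, power of 0.90 and 20% attrition. A two-sided test is assumed.

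- Difference: 69.80 − 48.17 = 21.63.
- Common SD: √((20.61² + 23.38²)/2) = 22.04.
- n per arm: 2 × (22.04 × (1.960 + 1.282)/21.63)² = 21.8, so 22.
- Attrition: 44/0.8 = 55, raised to 56, or 28 per arm.

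The stated sample size reproduces. By normal approximation, power is 0.957 at 28 per arm and 0.902 at 22. Losses within the attrition allowance therefore do not threaten power; the issue is bias.

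**3. Shift in one arm's mean**

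Assume that k of 28 women are removed from one arm, each 1 SD below that arm's mean, and none from the other arm. The mean of those remaining rises by 22.04 × k/(28 − k).

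| k | Shift (points) | Share of 21.63 |
|---|---|---|
| 1 | 22.04 × 1/27 = 0.82 | 4% |
| 2 | 22.04 × 2/26 = 1.70 | 8% |
| 3 | 22.04 × 3/25 = 2.64 | 12% |

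**4. Bias in the group difference**

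Let eT and eC be the shares removed from the hypnotherapy and control arms, and let removed women score L points below those retained. With no true effect, the bias is (eT − eC) × L. For L of 10 to 20 points:

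| eT | eC | Bias (points) |
|---|---|---|
| 10% | 10% | 0 |
| 15% | 5% | 1 to 2 |
| 20% | 5% | 1.5 to 3 |
| 20% | 0% | 2 to 4 |

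Swapping eT and eC reverses the sign. The removal shares and L are assumptions; the article gives no figure for either.

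**5. Size against sampling error**

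The standard error of the difference is 22.04 × √(1/28 + 1/(28 − k)), about 6 points. The shifts in step 3 are 0.14, 0.28 and 0.44 standard errors. With no true effect they would move the two-sided type 1 error from 0.05 to about 0.052, 0.059 and 0.072.

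**The case against.** The strongest reply is that Section 2.4.1 never says data are deleted, and that Section 2.11 is the only place that defines the analysis set. Read together, a woman who meets the criterion might stop taking part and still be analysed, and the randomised comparison would survive. An article may also leave the follow-up of withdrawn women to a fuller document. The first part stands as far as it goes: a reader might infer that the plan already breaks the randomised comparison, and the text does not establish that. What remains is that exclusion ordinarily means leaving the study, and that the two stated rules are not reconciled. That is a conflict within the article, not an omitted detail.

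A reader might also infer that controls have no visits at which an event could come to light. The article does not support this. Section 2.10, on both groups, and Section 2.15 refer to checks made at each session, and Section 2.10.2 has controls complete the questionnaires at the same stages. Only greater contact in the hypnotherapy arm is conceded, which makes unequal detection plausible but does not prove it.

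Finally, the illustrated shifts are modest beside both the planned difference and the standard error, and they assume no removals in the other arm. This is correct. The need to reconcile the sections rests on the conflict itself, not on the illustration.

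**Conclusion.** The point holds as a conflict between Sections 2.4.1 and 2.11 that must be resolved. An event that can occur only after allocation is listed as an exclusion criterion, while all randomised women are to be analysed. Bias arises only if the exclusion is carried out by removing women from follow-up or analysis.

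Its direction is conditional: towards hypnotherapy if more women are removed from that arm, near zero if removals match in number and depth, and against hypnotherapy if more controls are removed. Its actual size cannot be computed from the article. The 0.8 to 2.6 points rest on assumed removals from one arm only and an assumed depth of 1 SD.

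A reader might go further and conclude that the result is bound to favour hypnotherapy, or that the damage could not be undone in the analysis. The first requires unequal removal, which is not shown. The second requires outcome collection to stop, which Section 2.4.1 does not state. If questionnaires continue, applying Section 2.11 as written keeps these women in the comparison.

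**What to change.** Reconcile Section 2.4.1 with Section 2.11:

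- Remove the during-intervention event from the exclusion criteria as a reason to leave follow-up or analysis. No new pre-randomisation eligibility rule is needed.
- State that such events are recorded in the same way in both arms at the questionnaire time points.
- State that these women continue the planned questionnaires and stay in the intention-to-treat analysis.
- Label any analysis without them as a sensitivity analysis only.

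Whether such a woman continues sessions is a clinical matter for the investigators, and the amendment should leave it open.

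The cost is a documented amendment, agreed by the research team and approved by the Ethics Committee as Section 2.12 requires, and slightly more outcome variance. The questionnaires are already planned in both arms. The Consent section describes sampling as ongoing, so an early change protects outcome data still to be collected.

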### Sample Size and Sampling Method

2.5

#### Sample Size

2.5.1

According to Fathi et al.'s study [41], the average resilience in the control group was 48.17 ± 20.61, and in the intervention group was 69.80 ± 23.38. By applying these findings and taking into account a type 1 error of 0.05 and a test power of 0.90, the sample size for every group was calculated using the following formula:

Therefore, 22 people in each group and a total of 44 people will enter the study. But considering that in this study, resilience is measured in three stages (before the intervention, right after the intervention, and 4 weeks post‐intervention). The samples may have dropped. For this problem, the final sample volume was determined with a 20% drop:

The total sample size was 55, considering the 20% attrition, and as regards, we have two groups, so we considered the total sample size to be 56 people. Therefore, 28 samples are included in the study in each group (intervention and control).

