### Statistical Analysis

2.13

The data from quantitative variables will be described by calculating the mean ± standard deviation, and qualitative variables will be described in terms of frequency and percentage. To compare variables between intervention and control groups according to the qualitative and quantitative variable nature, the *χ*
^2^ test (if the default is not established, Fisher's exact test) and *t*‐test of two independent samples, analysis of variance, or its non‐parametric equivalent (Mann–Whitney and Kruskal–Wallis) will be used, respectively. It should be noted that checking the defaults in terms of normality (Kolmogorov–Smirnov and Shapiro–Wilk test) and equality of variances (Levene and F test) will be on the agenda. Finally, to compare the mean resilience score between the two intervention and control groups during the study period (before the intervention, right after the intervention, and 4 weeks post‐intervention), and also to control for the effect of intervening factors, repeated measures ANOVA or mixed models will be used for variance analysis. For every outcome, the projected effect size along with its 95% confidence interval will be displayed. The significance level of the tests will be 0.05. The analysis will be conducted using SPSS V.26. The reporting of statistical results will adhere to the Statistical Analyses and Methods in the Published Literature (SAMPL) guideline [53].

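### The 0.90 power is for a single two-group comparison, but resilience is to be compared over three times including baseline with the tested effect left open; on assumed correlations of 0.4 to 0.7 power runs from 0.66 to 0.99

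*Protocol article*

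**What the plan says.** Section 2.5.1 (Sample Size) takes its inputs from an earlier study: "the average resilience in the control group was 48.17 ± 20.61" and "in the intervention group was 69.80 ± 23.38". The calculation is made "taking into account a type 1 error of 0.05 and a test power of 0.90", and it concludes: "Therefore, 22 people in each group and a total of 44 people will enter the study". A 20% allowance for attrition raises the total to 55, made even at 56, or 28 per group. Whether the 5% level is one- or two-sided is not stated.

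Section 2.9.1 makes resilience the primary outcome. Section 2.13 (Statistical Analysis) names the two-sample t-test, with Mann–Whitney as the non-parametric equivalent, for simple comparisons between groups. It then names repeated measures ANOVA or mixed models "to compare the mean resilience score between the two intervention and control groups during the study period", and lists the three times as before the intervention, right after it and 4 weeks later. It does not say whether the group effect or the group-by-time effect decides the primary question, and no within-person correlation appears anywhere in the article.

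**The concern.** The sample size formula describes one comparison of two means at one time. The final resilience analysis is a different object, a model over three measurements in which baseline is one of the outcome times. Randomisation makes the expected baseline difference zero. If the two groups' mean scores over the whole period are compared, that zero is averaged in and the expected difference shrinks to two thirds of the one used for sizing. A test of group-by-time does not dilute the effect in this way, but its power depends strongly on the correlation between visits.

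The 0.90 is therefore attached to a calculation that does not correspond to the model named for the primary outcome. If the diluted effect were taken as the result, a null finding could be given more weight than the design supports.

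**Working it through.** **Inputs from section 2.5.1.** Means 48.17 and 69.80, so the difference is 21.63. SDs 20.61 and 23.38, so the pooled SD is √[(20.61² + 23.38²)/2] = 22.04 and d = 21.63/22.04 = 0.981. Alpha 0.05, power 0.90, 22 per group, 28 per group enrolled.

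**Reproducing the plan's figure.** n = 2(1.960 + 1.282)²/0.981² = 21.8, rounded up to 22 per group. Then 44/0.8 = 55, made even at 56. This needs a two-sided 5% level; one-sided gives 18. By the same formula, power at 22 is 0.902. The arithmetic is sound.

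**Exact t-test.** Noncentrality is d√(n/2). At n = 22 with 42 df, power is 0.889; at n = 23 it is 0.902; at n = 28 it is 0.950. So 0.90 needs 23 completers per arm: 23/28 = 82.1%, a loss of at most 17.9%.

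**Three-visit analysis.** The article gives no correlation, so the following is assumed: compound symmetry with within-person correlation r, no expected baseline difference, and the full 21.63 at both later visits.

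- *Group effect over three visits.* Expected difference (0 + 21.63 + 21.63)/3 = 14.42. SD of a woman's three-visit mean is 22.04√[(1 + 2r)/3]. The standardised effect is 0.981 × (2/3)/√[(1 + 2r)/3]. At r = 0.5 this is 0.801, and power is 0.738.
- *Group-by-time.* F test on 2 and 2(2n − 2) df with noncentrality (n/3)d²/(1 − r). At r = 0.5 and n = 22 this is (22/3)(0.963)/0.5 = 14.1 on 2 and 84 df, and power is 0.921.
- *Baseline-adjusted difference at one post-intervention visit.* Standardised effect d/√(1 − r²), giving up 4 further df (for example baseline 1, marital status 1, three BMI bands 2). At r = 0.5 this is 1.133, and power is 0.956.

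| Test | n per arm | r = 0.4 | r = 0.5 | r = 0.6 | r = 0.7 |
|---|---|---|---|---|---|
| Group effect, baseline averaged in | 22 | 0.781 | 0.738 | 0.697 | 0.659 |
| Group-by-time | 22 | 0.864 | 0.921 | 0.967 | 0.993 |
| Baseline-adjusted, one visit | 22 | 0.933 | 0.956 | 0.977 | 0.993 |
| Group effect, baseline averaged in | 28 | 0.874 | 0.838 | 0.802 | 0.767 |
| Group-by-time | 28 | 0.938 | 0.971 | 0.991 | 0.999 |

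**Sensitivity to r at 22 per arm.** From r = 0 to r = 0.9 the group effect falls from 0.957 to 0.593, while group-by-time rises from 0.643 to above 0.99. At r = 0.2 the baseline-adjusted effect is 0.981/√0.96 = 1.002, with power 0.90 (0.899 after the 4 df).

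**The case against.** The strongest reply is that nothing in section 2.5.1 is miscalculated. The 22 reproduces, and the step from 0.902 to 0.889 is the ordinary difference between the normal approximation and the noncentral t. It is worth one woman per group and is far smaller than the uncertainty in a d of 0.98 borrowed from one study. That stands. A reader might infer that the stated 0.90 is false; the article does not support that.

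A reader might also infer that the trial has only 66% to 78% power. Section 2.13 does not name the group effect, and section 2.14 speaks of measuring changes in resilience, which points at least as much to group-by-time. On the same assumptions group-by-time exceeds 0.90 at correlations of 0.5 and above. At low correlations even the group effect is adequately powered. That objection also stands: the low figures hold only for one choice of effect and for moderate to high correlation.

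Nor is a lower figure for Mann–Whitney (0.874 at 22 per arm, simulated on normal data) the plan's operating power. That test is the fallback for data that fail the assumption checks.

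The 22 is the number left after the full planned loss; with all 28 retained the t-test has 0.950. This does not remove the problem for the group effect, which at 28 per arm still stays below 0.90 at correlations of 0.4 to 0.7.

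Finally, the choice of primary effect may be settled in a full protocol or analysis plan that is not shown. What the article itself does is list baseline among the times compared while quoting a power for a different comparison. That is why the point is kept, but only as a minor one.

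**Conclusion.** The point holds in a limited form. The stated sample size is correctly derived for a single two-group comparison, with a shortfall of about one percentage point by the exact t-test. The substantive weakness is that this power is not tied to the resilience analysis described in section 2.13, where the tested effect is open and baseline counts as an outcome time. Depending on that choice alone, power at 22 completers per arm lies anywhere from 0.66 to 0.99 for correlations of 0.4 to 0.7.

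That range rests on compound symmetry, the full 21.63 difference at both later visits and the assumed correlations, none of which come from the article. It shows what the open choice is worth; it does not show that the trial is underpowered. Importance is low, because the remedy is a matter of wording.

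**What to change.** Enrol no more women. In section 2.13, make the primary test the between-group difference in post-intervention resilience adjusted for baseline, with baseline as a covariate and not as an outcome time, and name the post-intervention visit it refers to. State that the group effect averaged over all three visits is not the primary test. The repeated measures model can remain as a description of the course over time.

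In section 2.5.1, state that the test is two-sided and that 22 completers per arm give about 0.89 for the unadjusted t-test, with 0.90 reached if loss from 28 per arm is at most 17.9%. Add that at least 0.90 is expected for the baseline-adjusted contrast if the correlation with baseline is about 0.2 or more.

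The cost is a few sentences. The adjustment uses a baseline questionnaire that is already planned. The unadjusted power figure becomes one point less favourable.
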